
**Figure 4 figure4:**
[figure not shown]
MedBridge GO smartphone app.

#### Brief Aim-Specific Outcomes and Measurement

##### Sociodemographic and Health Characteristics

We are assessing sociodemographics (age, sex, race/ethnicity, etc) and cancer-related and general health history using our Screening and Baseline Surveys as well as chart reviews before/during Baseline Testing Session Part 1.

##### Cerebrovascular and Cognitive Function as Well as Cardiometabolic, Proinflammatory, and Epigenetic Outcomes

Part 2 of Baseline and Poststudy Testing involves participants coming to one of the study laboratories (Oklahoma City, Oklahoma) following an 8-hour fast, 12 hours of caffeine abstinence, and 24 hours of no alcohol, vitamins, other health supplements, or nonsteroidal anti-inflammatory drug use. They may continue taking medications aligned with health conditions. Participants are also required not to have exercised intensely in the last 24 hours. During this session, participants first complete blood pressure measurements and then blood and saliva sample collections. Blood samples are being collected through traditional venipuncture of the antecubital vein by trained study personnel. Samples are immediately processed and stored at –80 °C. From these blood samples, we assess high- and low-density lipoprotein and total cholesterol, and fasting blood glucose, among other outcomes, using the Lipid Panel+ kit of Piccolo Xpress (Abbott, Chicago, Illinois). Further, we will use enzyme-linked immunosorbent assays to assess high-sensitivity C-reactive protein as well as interleukin-6 and monocyte chemoattractant protein 1—analyses to be run nearer the end of the study to ensure minimal batch effects. These data will allow us to measure cardiometabolic and proinflammatory cytokines aligned with CICI and T2DM pathophysiology [10,11,21]. Finally, we collect saliva with a DNA Genotek OMNIgene Saliva DNA and RNA collection kit (OMR-610; Ottawa, Ontario). Participants spit 1 mL of saliva into the collection tube to a marked fill line, snap the tube closed, and provide it to research staff, after which it is stored at –80 °C. For the purposes of this study, genomic DNA isolations will be performed from whole blood and saliva for epigenetic analyses, namely, DNA methylation. Similar to the enzyme-linked immunosorbent assays, epigenetic analyses will also take place nearer to the end of the study in order to randomize samples to minimize batch effects.

We use the National Institutes of Health Toolbox [73,74] to deploy a standardized cognitive battery following blood and saliva collection and after participants have had the opportunity to have a snack of their choice. This testing includes the following five tests: (1) Dimensional Change Card Sort (executive function); (2) Pattern Comparison Processing Speed; (3) List Sorting Working Memory; (4) Flanker Inhibitory Control and Attention; and (5) Picture Sequencing Memory. These tests will be analyzed per established standards [75,76] to yield a Fluid Composite Score—standards used validly in similar studies examining how exercise impacts the cognitive function of middle-aged and older adults with mild cognitive impairment [77].

We are completing cerebrovascular function and select cardiometabolic outcome measurements during Part 3 of Baseline and Poststudy Testing within a second study laboratory (Norman, Oklahoma). Participants come to this Testing Session following the same fasting and “no exercise” requirements as Part 2 of Baseline and Poststudy Testing (above). We first measure height, weight, and waist and hip circumference, and complete a pregnancy test, if needed. Participants then complete transcranial doppler (TCD) measurements using 2MHz pulse-wave probes and a headpiece (Nuerovision Transcranial Doppler Ultrasound, Multigon Industries, Elmsford, New York). We then have participants complete a test of cerebrovascular reactivity to CO_2_. This test involves participants breathing through a facemask connected to a 3-way sliding valve connected to a meteorological balloon filled with a safe medical-grade gas mixture (CO_2_= 3%, O_2_= 40%, N_2_= 57%) until their partial pressure of end tidal CO_2_ reaches 10 mmHg above baseline levels (takes ≈2 minutes). We complete 2 trials separated by 5 minutes of rest, averaging data across trials per established standards [78,79]. Then, participants’ dynamic cerebral autoregulation is assessed via the Thigh Cuff Release Challenge technique [80]. Large bilateral blood pressure thigh cuffs are rapidly inflated (rapid cuff inflation/deflation system; D.E. Hokanson, Inc., Bellevue, Washington) to occlude the lower limbs. Blood flow is monitored in the dorsalis pedis artery, and the initial thigh cuff pressure starts at 20 mmHg above systolic blood pressure. If blood flow is still detected, thigh cuff pressure increases gradually until occlusion is confirmed. The occlusion is held for 2 minutes. After 2 minutes of occlusion, the cuff pressure is rapidly deflated [80]. Both of these tests are completed while the participant is in a supine position. A second set of TCD measurements is then made while participants engage in a graded exercise protocol on a recumbent bike (Lode Corival Recumbent CPET; Groningen, The Netherlands) to assess fitness. This graded exercise protocol starts with 3 minutes of baseline rest. Following this rest period, the protocol then begins at 20W and increases by 20W increments every 3 minutes until volitional exhaustion or the inability to maintain at least 50 revolutions per minute on the bike. Participants report their rating of perceived exertion at the end of every 3-minute stage (0=no exertion; 10=maximal exertion).

The above measurements provide the following metrics: middle cerebral artery velocity and cerebrovascular resistance, conductance, and pulsatility indexes. As cerebral blood pressure autoregulation difficulties can result from mechanisms underlying CICI [25], we will also use transfer function analysis of TCD measurements, as well as the autoregulation index, to measure dynamic cerebrovascular autoregulation. Analyses will be performed using the most recent Cerebrovascular Research Network recommendations [81]. Other relevant measurements generated during this testing include (1) heart rate calculated by R-R intervals using a Bluetooth II-lead ECG (EQ Life Monitor, Equivital Limited, Cambridge, United Kingdom); (2) mean arterial blood pressure, cardiac output, stroke volume, and total peripheral resistance measured via finger photoplethysmography (Finapres NOVA, Finapres Medical Systems B.V, Enschede, The Netherlands); (3) prefrontal cortex oxygen saturation assessed using wireless near-infrared spectroscopy using a small probe placed unilaterally on the right-side of the forehead (Portalite, Artinis Medical Systems, Elst, The Netherlands); (4) arterial blood oxygenation evaluated using finger-tip oximetry on the right index finger (Oximeter pod, ADInstruments, Sydney, New South Wales, Australia); and (5) end-tidal CO_2_, partial pressure end-tidal CO_2_, and maximum oxygen consumption collected and analyzed via a gas analyzer and pneumotachometer on a breath-by-breath basis (Gemini End-Tidal O_2_ and CO_2_ Analyzer, CWE Incorporated, Ardmore, Pennsylvania).

##### SCT-related Construct, Psychosocial, HRQoL, and PA Outcomes

We are measuring all Aim 3 outcomes during Part 1 of participants’ Baseline and Poststudy Testing Sessions, as well as during Midpoint Testing. The exception is PA, which is only measured at Baseline and after the 12th study week. We are assessing SCT-related psychosocial outcomes using validated surveys delivered via REDCap. Self-efficacy is being assessed using a 9-item measure from Rodgers et al [82]. Participants are noting their confidence during different PA-related situations (“0%: Not confident at all” to “100%: Extremely confident”; 10% increments). Social support is being evaluated using the Social Support and Exercise Survey, with participants reporting frequency of PA support over the last 3 months from family and, separately, friends (“1: None” to “5: Very often”) [83]. PA-related enjoyment is being measured via the 18-item Physical Activity Enjoyment Scale [84], with feelings related to PA-related statements/situations reported on a 7-point scale (varied response options). We are using a 14-item scale [85] to assess agreement between hypothetical PA barriers and participants’ perceived barriers (“1: Strongly disagree” to “4: Strongly agree”). Last, we are using the 13-item Outcome Expectations for Exercise Scale-2 [86] to assess agreement with listed positive and negative benefits of PA (“1: strongly agree” to “5: strongly disagree”).

We are assessing stress, anxiety, mood, and depressive symptoms and HRQoL using validated instruments. We are measuring chronic stress with the 10-item Cohen Perceived Stress Scale [87]. Participants report stress frequency over the last month (“0: Never” to “4: Very often”). We measure chronic anxiety with the State-Trait Anxiety Inventory [88,89], which includes 20 items, each on state and trait anxiety (“1: Almost never” to “4: Almost always”). Chronic mood is being assessed by the Positive and Negative Affect Scale [90]. This scale has 10 items, each for positive and negative affect (“1: Very slightly or not at all” to “5: Extremely”). Chronic depressive symptoms are being assessed by the 9-item Patient Health Questionnaire-9 [91] (“0: Not at all” to “3: Nearly every day”). For HRQoL, the following components of physical and psychological health are being assessed using the Patient-Reported Outcomes Measurement Information System: physical functioning, fatigue, anxiety, depression, pain interference, pain intensity, sleep impairment, and sleep disturbance [92,93]. Measurements are on a 5-point scale, with 5 being the worst on all components aside from physical function, where higher scores are better.

We are assessing PA between Baseline Testing Session Parts 2 and 3 and just after the 12th study week with ActiGraph wGT3X-BT accelerometers—valid for free-living PA assessments [94]. Established protocols for placement and wear duration are being followed by participants [95], and accepted thresholds (≥10 hours/day of wear time; at least 4 days, including one weekend day) are used to clean these data. Established cut points will be used to analyze PA durations per day [96]. Daily average minutes of moderate-to-vigorous PA, light PA, and sedentary behavior will be reported.

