Characterize cerebrovascular function, cognitive function, proinflammatory cytokines, and cardiometabolic outcome differences between cancer survivors with and without T2DM. We hypothesize that cancer survivors with T2DM will have (1) poorer measures of middle cerebral artery velocity and cerebrovascular conductance, reactivity, and resistance; (2) lower executive function scores; (3) higher C-reactive protein, interleukin-6, and monocyte chemoattractant protein 1 concentrations; and (4) higher blood pressure and insulin resistance.

### Specific Aim 2

Examine pre- to post-PA program differences for changes in Specific Aim 1’s outcomes between cancer survivors with and without T2DM. We hypothesize that greater pre- to post-PA program improvements in these outcomes will be observed for cancer survivors with T2DM.

### Specific Aim 3

Assess pre- to post-PA program differences for changes in Social Cognitive Theory–based (SCT-based) [58,59] constructs, select psychosocial outcomes, HRQoL, and PA between cancer survivors with and without T2DM. We hypothesize that cancer survivors with and without T2DM will demonstrate pre- to post-PA program improvements in (1**)** SCT-based, PA-related self-efficacy, outcome expectations, enjoyment, social support, and barriers; (2) stress, anxiety, mood, and depressive symptoms, and that cancer survivors with T2DM will have greater improvements than cancer survivors without T2DM; (3) in HRQoL due to greater improvements in physical functioning as well as pain intensity/interference, and (4) overall PA participation due to greater increases in light and moderate PA.

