### Statistical Analyses

We will first inspect all data for outliers/errors and normality, with analyses done in SPSS (version 29; IBM Corp) and R (R Foundation), depending on the metrics being analyzed. Baseline differences between cancer survivors with and without T2DM for (1) sociodemographics, (2) health characteristics, and (3) Aim 1/Exploratory outcomes (ie, cerebrovascular and cognitive function, cardiometabolic outcomes, proinflammatory cytokines, epigenome) will be compared using *t* tests or chi-square tests, as appropriate. Repeated measures ANOVA will analyze between-group differences for changes in Aim 1/Exploratory outcomes during the PA program (Aim 2) and Aim 3 outcomes (ie, SCT-related constructs, psychosocial outcomes, HRQoL, PA). If any sociodemographic or health characteristics differ at baseline between cancer survivors with and without T2DM, we will use repeated measures ANCOVA. Consistent with recommendations for pilot research [97,98], no a priori power analyses have been performed. Indeed, this study is designed to generate the data necessary to develop larger, properly powered, and federally funded studies on this critical topic.

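### Light PA and sedentary time are compared as daily minutes with no allowance for accelerometer wear time, so any change in wear between visits can pass into the measured change in activity

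*Protocol article*

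**What the plan says.** The section on SCT-related, psychosocial, HRQoL and PA outcomes sets out the accelerometer outcome in four steps.

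- Timing: "The exception is PA, which is only measured at Baseline and after the 12th study week". There are therefore two measurements per participant.
- Wear instructions: "Established protocols for placement and wear duration are being followed by participants". A source is cited, but its content is not given.
- Valid days: "accepted thresholds (≥10 hours/day of wear time; at least 4 days, including one weekend day) are used to clean these data".
- Metric: "Established cut points will be used to analyze PA durations per day", followed by "Daily average minutes of moderate-to-vigorous PA, light PA, and sedentary behavior will be reported".

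Under Statistical Analyses, "Repeated measures ANOVA will analyze between-group differences for changes in Aim 1/Exploratory outcomes during the PA program (Aim 2) and Aim 3 outcomes", and PA is listed among the Aim 3 outcomes. Covariates enter by one rule: "If any sociodemographic or health characteristics differ at baseline between cancer survivors with and without T2DM, we will use repeated measures ANCOVA". The Abstract names repeated-measures ANCOVA for change over time but lists no covariates.

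The PA hypothesis under Specific Aim 3 expects improvement in "overall PA participation due to greater increases in light and moderate PA" in the T2DM group. It does not mention sedentary time.

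**The concern.** An accelerometer records minutes of light or sedentary behaviour only while it is worn. The article sets a lower limit for a valid day, but no upper limit, fixed window or common day length. A day with 10 hours of wear and a day with 14 hours each count as one day, and the longer one will normally contain more light and more sedentary minutes.

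The stated model does not correct for this. Wear time is neither a sociodemographic nor a health characteristic. A covariate chosen because the groups differ at baseline also could not represent a change in wear from Baseline to Poststudy.

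Two comparisons are exposed. The pre-post change has no control group, as the limitations section acknowledges, so a shift in wear common to everyone could look like an effect of the program. The between-group comparison of change is biased only if the wear change differs by T2DM status. Separately, ordinary variation in wear between visits widens the SD of change. That matters in a pilot whose declared purpose is to supply data for designing larger trials.

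**Working it through.** **Inputs from the article.** Valid day of at least 10 hours; outcome in minutes per day; two visits; 15 participants per group, 30 in all. The only sample-size figure is the accrual target: 30 / (1 - 0.20) = 37.5, rounded up to 38. It reproduces, and this point does not depend on it. The article gives no wear times, activity fractions, SDs or effect sizes, so everything below that uses them is an assumption.

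**1. Shift per hour of wear.** If behaviour is unchanged and a category takes up a fraction f of wear, then apparent change (min/day) = f × 60 × change in wear (h). For a change of 1 hour:

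| Category | Assumed f | Apparent change per hour |
|---|---|---|
| Light PA | 0.25-0.40 | 15-24 min/day |
| Sedentary | 0.50-0.70 | 30-42 min/day |
| MVPA | 0.05 | 3 min/day |

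For valid days of different length, at f = 0.35 for light PA, 10 hours gives 0.35 × 600 = 210 min and 14 hours gives 0.35 × 840 = 294 min.

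**2. Noise when mean wear is equal.** Assume mean wear of 13 h, an SD of 1.2 h at each visit (independent between visits), light PA at 33% of wear, and a within-person SD of change in that share of 4 percentage points.

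- Behavioural part: 0.04 × 13 × 60 = 31.2 min.
- Wear part: 1.2 × √2 × 60 × 0.33 = 33.6 min.
- SD of change in minutes: √(31.2² + 33.6²) = 45.9 min.

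Simulation with these inputs gives an average sample SD of about 45 min for minutes and about 31 min after standardising to 13 h. The variance ratio is (45.9 / 31.2)² = 2.2.

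**3. False positives in the group comparison.** Same inputs, no true change in behaviour, 15 per group, two-sided 5% level. Standard error = 45.9 × √(2/15) = 16.8 min.

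| Group difference in wear change | False light PA difference | Rejection rate, minutes |
|---|---|---|
| 0 h | 0 | 5% |
| 0.5 h | 0.5 × 60 × 0.33 = 10 min | about 9% |
| 1 h | 20 min | about 20% |
| 1.5 h | 30 min | 37-40% |

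A normal approximation with f = 0.35 and an assumed SD of change of 40-80 min gives 30% down to 11% for a 1-hour difference.

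**4. False positives in the pre-post comparison.** If all 30 participants wear the device 1 hour longer at Poststudy, the apparent change at f = 0.35 is 21 min. With an SD of change of 40-80 min, the standard error is 40/√30 = 7.3 to 80/√30 = 14.6 min, and the rejection rate is about 82% down to 30%.

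**5. Is percent of wear always better?** No. Take 10 hours of wear at 35% light (210 min) and add 2 evening hours at 10% light (12 min). Minutes go from 210 to 222, a change of +12. The share goes from 35% to 222/720 = 30.8%, which is (0.308 - 0.35) × 13 × 60 = about -32 min when standardised to 13 h. Here the share is further from the truth than the minutes. The simulation in step 3 keeps the share at a 5% error rate because it generates light PA as a constant fraction of wear.

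**The case against.** The strongest reply is that a condensed article leaves accelerometer processing to the full protocol, that nothing in the text says the minutes are unadjusted, and that participants follow a cited protocol for wear duration. If that protocol asks for a fixed or near-complete wear period, much of the variation disappears.

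Part of this stands. The cited protocol is not shown, and it may limit the variation in wear. But the article does more than stay silent. It fixes the metric as minutes, fixes the validity rule as a lower limit, and fixes a covariate rule that excludes wear time. Wear instructions influence how long participants wear the device; they do not change how the minutes are analysed.

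Three stronger readings are tempting and are not supported.

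- A reader might infer that a false PA difference between groups is to be expected. That needs the wear change to differ by T2DM status. Nothing in the article suggests this, and with no differential the error rate of the group test stays at 5%.
- A reader might infer that the whole PA hypothesis is compromised. MVPA moves by only about 3 min/day per hour of wear, and sedentary time has no stated hypothesis, so the exposure lies mainly in light PA.
- A reader might infer that percent of wear is simply the correct metric. Step 5 of the working shows that it fails when the added hours have a different activity mix.

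It is also fair to say that false-positive rates carry limited weight in a pilot with no power analysis. The extra noise and the uncontrolled pre-post comparison are not answered by that.

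**Conclusion.** The point holds in a conditional form. As written, the plan lets a change in wear time pass into the analysed change in light PA and sedentary minutes, and its covariate rule would not remove it. The shift is about 15-24 min/day of light PA per hour of wear change if light PA is 25-40% of wear. It affects the pre-post comparison whenever mean wear changes, and the group comparison only when that change differs by group. The loss of precision needs only ordinary visit-to-visit variation: an SD of change of about 45 against 31 min, given a wear SD of 1.2 h per visit and the other inputs in step 2.

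All these sizes rest on assumed fractions and SDs, and the actual effect in this study cannot be determined from the article. It is a worthwhile correction to one component of one Aim 3 outcome, not a threat to the study as a whole.

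**What to change.** Keep daily minutes as the reported outcome. For light PA and sedentary time, analyse change with adjustment for visit-specific wear time: either a mixed model with wear as a time-varying covariate or, with only two visits, a change-score model with change in wear as a covariate. Present percent of wear time as a sensitivity analysis, stating that it assumes unworn hours have the same activity mix as worn hours. Report mean wear time and number of valid days by group and visit, so that readers can judge whether wear shifted at all.

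The cost is a few sentences in the analysis plan and one extra model term in a small sample. No new data are needed, because daily wear time has to be computed to apply the 10-hour rule. Recruitment is expected to run until late 2026, so the change can be fixed before the Poststudy data are analysed.

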### Statistical Analyses

We will first inspect all data for outliers/errors and normality, with analyses done in SPSS (version 29; IBM Corp) and R (R Foundation), depending on the metrics being analyzed. Baseline differences between cancer survivors with and without T2DM for (1) sociodemographics, (2) health characteristics, and (3) Aim 1/Exploratory outcomes (ie, cerebrovascular and cognitive function, cardiometabolic outcomes, proinflammatory cytokines, epigenome) will be compared using *t* tests or chi-square tests, as appropriate. Repeated measures ANOVA will analyze between-group differences for changes in Aim 1/Exploratory outcomes during the PA program (Aim 2) and Aim 3 outcomes (ie, SCT-related constructs, psychosocial outcomes, HRQoL, PA). If any sociodemographic or health characteristics differ at baseline between cancer survivors with and without T2DM, we will use repeated measures ANCOVA. Consistent with recommendations for pilot research [97,98], no a priori power analyses have been performed. Indeed, this study is designed to generate the data necessary to develop larger, properly powered, and federally funded studies on this critical topic.

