**Methods:**

We are conducting a 30-participant pilot study in cancer survivors with (n=15) and without (n=15) T2DM—all of whom report currently experiencing “chemo-brain.” To account for attrition, we are recruiting 38 cancer survivors from Oklahoma City, OK, and the surrounding area. Among the most important eligibility criteria are the self-report of cognitive difficulties following primary cancer treatment, being ≥18 years old, being within 3 years of primary cancer treatment, and not meeting nationally recommended PA guidelines. Participants receive 2 smartphone apps. One smartphone app provides health education and the ability to set goals and journal about their wellness journey. The other provides a workout program continually tailored to each participant via their communication with the study exercise physiologist, with resistance bands and a wearable device provided to support the program. At Baseline and Poststudy, we assess cerebrovascular function (transcranial doppler [TCD]), cognition (National Institutes of Health Toolbox), cardiometabolic outcomes (venipuncture), and epigenetics (saliva collection). Participants also wear accelerometers at Baseline and Poststudy to objectively assess PA, with Baseline, Midpoint, and Poststudy surveys assessing psychosocial outcomes. We will use *t* tests and chi-square tests to assess baseline differences and repeated-measures ANCOVA to assess changes over time.

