Aerobic physical activity (PA) and resistance training (RT) have robust health benefits counteracting much of the pathophysiology underlying CICI and T2DM [42,43]. Reviews [44,45] suggest better cerebrovascular function in those who are more active or fitter relative to those who are less active or fit, with greater fitness positively associated with cognitive function in other at-risk populations [46,47]. In those with T2DM, research has shown that PA is impactful at lowering proinflammatory cytokines [42,48-50] and improving insulin sensitivity [51,52]. Yet, research is needed on how increasing PA in cancer survivors with T2DM reporting CICI improves cerebrovascular and cognitive health through improved fitness. Notably, cancer survivors prefer supportive, individualized, home-based PA programming that includes RT and aerobic activities such as walking [53]. Home-based programs are recommended by the American Cancer Society [54] given their ability to circumvent some of the barriers to PA program participation (eg, distance to clinic, lack of time) among those living with and beyond cancer. Smartphone app technology can assist in providing this home-based PA program access. Relative to routine care, smartphone app–based supportive care among cancer survivors has been observed to improve HRQoL, self-efficacy, and symptoms of distress and depression [55]. Further, multicomponent interventions that include personalized PA programming delivered via smartphone apps, with wearable devices to supplement behavior change, have shown promise for increasing PA among cancer survivors [56,57].

We are conducting a 30-participant pilot study in cancer survivors with T2DM (n=15) and without T2DM (n=15)—all self-reporting “chemo-brain”—that includes personalized PA programming and education delivered via 2 smartphone apps, with a wearable device provided for further behavior change support. We have detailed our Specific Aims and Hypotheses below.

### Specific Aim 1

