## Methods

### Study Design and Recruitment

We are conducting a National Institutes of Health Stage 1 trial [60], and we have registered this trial on ClinicalTrials.gov (NCT06725953). Moreover, we used the SPIRIT (Standard Protocol Items: Recommendations for Interventional Trials)-Outcomes Guidelines to guide the construction of this manuscript [61]. We are recruiting individuals within Oklahoma City and the greater state of Oklahoma. Our accrual target is 38 participants to allow our desired number of 30 participants to be achieved when accounting for an anticipated 20% attrition rate [62]. We are conducting rolling recruitment and are recruiting via (1) emailed and posted flyers; (2) digital advertising to local survivorship groups; (3) oncologist referral; and (4) chart reviews/assistance from the Stephenson Cancer Center Clinical Trials Office. Potentially eligible individuals are sent a REDCap-based (Research Electronic Data Capture–based) screening survey, and, whenever possible, we are verifying cancer diagnosis, chemotherapy regimen, and T2DM status via medical records. We are evaluating individuals against stringent eligibility criteria. Specifically, our inclusion criteria are as follows: (1) 18 years or older; (2) ability to speak/read English; (3) ability to provide informed consent; (4) underwent treatment within the last 3 years for a non–brain-related cancer with said treatment having included chemotherapy and not currently undergoing any active cancer treatments (ongoing endocrine/hormonal therapy or immunotherapy, when either are used for maintenance purposes, are acceptable); (5) self-reported cognitive difficulties following cancer treatment; (6) (for cancer survivors with T2DM) current T2DM diagnosis as classified by a fasting blood glucose of ≥126 mg/dL, 2-hour oral glucose tolerance test of ≥200 mg/dL, HbA_1c_ level of ≥6.5%, or use of medications (eg, Metformin) or insulin to treat hyperglycemia or (for cancer survivors) no current T2DM diagnosis as classified by a fasting blood glucose <100 mg/dL, 2-hour oral glucose tolerance test <140 mg/dL, or HbA_1c_ level of <5.7%. Presence/absence of T2DM to be confirmed preferentially via physician’s documentation or via our measurement of participants’ fasting blood glucose during the blood draws within Part 2 of Baseline Testing (Figure 1); (7) own smartphone or computer with internet access; and (8) willing to participate in the 12-week remotely-delivered PA program. Our exclusion criteria are as follows: (1) reporting a Physical Activity Readiness Questionnaire score indicating PA may be unsafe unless a doctor’s note clearing a prospective participant for study participation can be provided; (2) engaging in ≥75 min/week of vigorous-intensity PA, ≥150 min/week of moderate-intensity PA, or an equivalent combination of both over the last 3 months; (3) currently undergoing active cancer treatment or planning more treatment within the next 3 months; (4) classified within the prediabetes range for their fasting blood glucose measurement (100-125 mg/dL) during Part 2 of Baseline Testing. Notably, those with T2DM verified via a physician’s documentation and who report the use of medications or insulin to treat hyperglycemia, who are found to be in the prediabetes range, will still be enrolled within the T2DM group and study. These results would indicate a participant with well-controlled T2DM, not prediabetes; and (5) currently a prisoner, pregnant, or planning to become pregnant during the study.

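### Non-randomized T2DM groups are compared without adjustment in Aim 1, and in Aims 2 and 3 covariates enter only if a baseline difference is found, a rule with little power at 15 per group

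*Protocol article*

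**What the plan says.** The protocol article plans for 15 completers with T2DM and 15 without, and allows for attrition: "Our accrual target is 38 participants to allow our desired number of 30 participants to be achieved". Group membership follows from the glycemic and treatment criteria under Study Design and Recruitment. That section describes no matching or stratification on age, sex or treatment history.

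The Statistical Analyses section then fixes three things:

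- **Aim 1 (baseline contrast).** "Baseline differences between cancer survivors with and without T2DM for (1) sociodemographics, (2) health characteristics, and (3) Aim 1/Exploratory outcomes" "will be compared using *t* tests or chi-square tests, as appropriate". No covariates are named.
- **Aims 2 and 3 (change).** The default model is unadjusted: "Repeated measures ANOVA will analyze between-group differences for changes in Aim 1/Exploratory outcomes during the PA program (Aim 2"), and the same model serves the Aim 3 outcomes.
- **Covariate rule.** "If any sociodemographic or health characteristics differ at baseline between cancer survivors with and without T2DM, we will use repeated measures ANCOVA". The section gives no criterion for a difference, no fixed covariates and no excluded variables.

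The Methods part of the abstract states "repeated-measures ANCOVA to assess changes over time" without the condition.

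**The concern.** Eligibility is broad: any adult, any non-brain cancer treated with chemotherapy, treated within the last three years. Age, sex, cancer type and time since chemotherapy could therefore differ between the two groups, and they may bear on cerebral blood velocity and cognition. Because the adjustment rule invokes a repeated-measures model, it does not reach the cross-sectional Aim 1 tests, which stay unadjusted whatever the baseline table shows. Aim 1 could then report an age or treatment effect as a T2DM effect.

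In Aims 2 and 3 the model depends on a baseline test that has little power for a real imbalance and that can also fire by chance. In the other direction, glucose-lowering drug use and diabetes history plausibly count as health characteristics. They differ between groups by design and nothing excludes them. Adjusting for them would remove part of the contrast under study.

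The study is meant to supply data for a larger trial, so a biased group difference would carry into that planning.

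**Working it through.** **Inputs from the article.** 15 completers per group; 38 accrued; 20% attrition. No effect size or SD is given ("no a priori power analyses have been performed"), and no alpha for the baseline tests.

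**Assumptions.** Two-sided alpha 0.05; one confounder whose group means differ by d SD; correlation r between confounder and outcome; no true group effect. The values of d and r below are illustrative.

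**1. The plan's own figure.** 30 / (1 − 0.20) = 37.5, rounded up to 38. This reproduces and is not at issue. It gives 38 / 2 = 19 per group at accrual.

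**2. Power of the baseline test.** Noncentral t with df = 2n − 2 and noncentrality d·√(n/2). For n = 15 and d = 0.5: noncentrality 0.5 × √7.5 = 1.37, critical value 2.05, power 0.26.

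| True imbalance | Power, n = 15 | Missed | Power, n = 19 | Missed |
|---|---|---|---|---|
| 0.5 SD | 0.26 | 74% | 0.32 | 68% |
| 0.7 SD | 0.46 | 54% | 0.56 | 44% |
| 0.8 SD | 0.56 | 44% | 0.67 | 33% |

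**3. Chance triggers.** With no real imbalance, the chance that at least one of k independent baseline tests is significant is 1 − 0.95^k: 23% for k = 5, 40% for k = 10, 64% for k = 20.

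**4. Aim 1: outcome at one time, unadjusted.** Bias = r × d = 0.5 × 0.5 = 0.25 SD. In simulation (8,000 replicates, 15 per group) the unadjusted test rejects a true null 10% of the time. Over r = 0.3 to 0.7 the range is 7–16% at d = 0.5 and 9–32% at d = 0.8. With the confounder prespecified as a covariate, rejection stays at 4.5–5.3% and the bias is 0.00.

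**5. Aims 2 and 3: change from before to after the program.** The target is the group difference in change, so only the confounder's effect on change matters. Simulation with pre and post values, d = 0.5, level slope 0.5 and assumed within-person residual correlation 0.6:

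| Confounder's effect on change | Bias, unadjusted | Bias, trigger rule | False positives, trigger rule |
|---|---|---|---|
| None (level only) | 0.00 | 0.00 | about 5% |
| 0.2 per SD | about 0.10 SD (0.2 × 0.5) | about 0.05 SD | about 5% |

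A hand check on the 0.05: in the single-time model with r = 0.5, the bias among replicates where the test missed the confounder was 0.168 SD. Scaling to a slope of 0.2 gives 0.168 × 0.2 / 0.5 = 0.067. Multiplying by the 74% of studies in which it is missed gives 0.050.

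**The case against.** The strongest defence is that this is a pilot. Aim 1 is worded as characterizing differences, for which an unadjusted description is legitimate, and the article concedes limited power. That supports keeping the unadjusted difference, but not having it alone. The Aim 1 hypotheses are directional, and the Background says that comparing those with and without T2DM may clarify how much T2DM contributes to the mechanisms. Low power is also what makes a test-based covariate rule work badly.

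Four stronger readings are tempting, and the documents do not support them.

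- **That the trigger leaves about 0.13 SD of bias in Aims 2 and 3.** That figure comes from an outcome at a single time. The trigger governs change, where a stable confounder of level cancels. It would apply only if the confounder acted on change as strongly as is assumed for level.
- **That the rule will adjust for glucose or HbA1c.** Fasting glucose is listed among the blood-based cardiometabolic outcomes, which the analysis section separates from health characteristics. HbA1c appears only as an eligibility criterion. The supportable statement is that drug use or diabetes history can enter. A 64% inflation of the group standard error, √(1 + 2.6²/4) = 1.64, rests on an assumed 2.6 SD separation of a marker.
- **That the groups are certain to differ in age, sex or treatment history.** The article gives no figures on this.
- **That the abstract seriously contradicts the methods.** It reads as a shortened form of the conditional rule. The mismatch is minor.

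**Conclusion.** The point holds in moderate form and should be fixed. Both the unadjusted Aim 1 comparison and the baseline-difference trigger are rules the article states, so this is not a detail left to an unseen analysis plan. That the trigger misses a 0.5 SD imbalance about three times in four rests only on the planned group size and a conventional 5% level.

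The consequences are conditional on assumed values. Aim 1 carries most of the harm, through bias in the group difference and a false-positive rate about double the nominal one in the illustrated case. For Aims 2 and 3 the effect is small or nil, and false positives are not materially inflated. The objection there is that the model is chosen by a weak and partly random test, with nothing to keep T2DM-defining variables out.

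**What to change.** - Delete the baseline-difference trigger.
- Name one short covariate set on subject-matter grounds, used in all aims whatever the baseline p values: for example age, sex and time since chemotherapy, the last if cancer history or chart review supplies it. Cancer type is a reasonable alternative, but with 30 participants the list must stay short.
- Aim 1: report the unadjusted difference alongside a linear model with group plus these covariates.
- Aims 2 and 3: use the same covariates with covariate-by-time terms.
- State that variables that define or treat T2DM are not covariates.
- Align the abstract with the Statistical Analyses section.

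The change is to analysis wording, best made before any group comparison is seen; the article expects to begin analyzing baseline data in early 2026. The statistical cost is about three degrees of freedom out of 30 − 2 = 28, leaving 25.
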